## 6. METHODS

### 6.1 Study parameters/endpoints

#### 6.1.1 Main study parameter/endpoint

The primary endpoint will be the time to death (overall survival (OS)) counted from the first date of ReRT until death due to any cause. Both treatments are finished within 2 to 3 weeks.

#### 6.1.2 Secondary study parameters/endpoints

The key secondary endpoint is:

- Progression free survival (PFS) counted from the first date of re-irradiation until the date of MRI evidence of tumor recurrence or death due to any cause. Agreement of the tumor board or a consultant neuro-radiologist that imaging changes are in keeping with recurrence and not radionecrosis is necessary.

Other secondary endpoints include the following:

- Recurrence Patterns on MRI.
- Radiation toxicity graded by CTCAE v5.0
- Anti-edema therapy (including Dexamethasone and Bevacizumab use).
- Health Related Quality of Life (HRQoL) prospectively monitored by EQ-5D-5L, EORTC QLQ-C15-PAL and EORTC-QLQ-BN20+2 questionnaires. (only for the experimental arm 1, cannot be analyzed retrospectively in the control arm 2).

#### 6.1.3 Other study parameters

In addition, KPS will be recorded in the experimental arm 1 and molecular analysis on prior surgically acquired tumor tissue, as well as at the time of recurrence (if available), will be performed.

### 6.2 Study procedures Arm 1

After obtaining informed consent (for details, see section 9.2), patients will receive treatment and necessary follow-up procedures. During the course of the study, participating centers will collect baseline characteristics, technical data such as MRI's, CT's and treatment plans and date of death. Medical imaging will be uploaded to a radiological database at a FTP server. Central data collection exists of HRQoL assessment, toxicity, anti-edema therapy and performance status. Central data collection will be performed by the study team by phone call, or via digital or paper questionnaires. Study procedures are summarized in Table 3. Patients will complete HRQoL questionnaires and the study team will record toxicity and anti-edema treatment by phone call at baseline and at 2, 4, 6, 13, 26, 39, and 52 weeks from the start of ReRT or until disease progression (whichever is sooner). During the first 6 weeks HRQoL will be assessed using the EQ-5D-5L. At subsequent time points QLQ-C15-PAL and BN20+2 will be completed digitally or on paper. Clinicians will be asked to record toxicity, KPS and anti-edema therapy use during regularly scheduled consults.

In case of suspicion of progression, recurrence or radionecrosis on MRI without consensus of diagnosis by the tumor board a FDG-PET, FET-PET or spectroscopy may be used to differentiate but is not mandatory.

IDH-1/2 mutation and MGMT-methylation will be determined at baseline using prior surgically acquired tissue, when molecular analysis has not been performed before, as well as at the time of recurrence (if available).

Any clinical follow-up data after 12 months will be uploaded at time of death, if known.

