## SUMMARY

**Rationale:** Re-irradiation is a generally accepted method for salvage treatment in patients with recurrent glioma. However, no standard radiation regimen has been defined.

Hypofractionation with dose-escalation will reduce patient's burden while maintaining the survival benefit.

**Objective:** To determine if re-irradiation in 4 fractions is non-inferior to 10 fractions in the primary endpoint of survival after re-irradiation. Secondary objectives are to establish and compare recurrence patterns, progression free survival, toxicity and anti-edema treatment and to describe health-related quality of life in the experimental arm.

**Study design:** RISING trial A was an open label, randomized, non-inferiority, phase III trial with 1:1 allocation for 130 patients among all participating centers. RISING trial B will be a phase II, multi-center, clinical trial with a historic control group.

**Study population:** Adults with unifocal recurrent high-grade glioma up to 125 cc eligible for re-irradiation.

**Intervention:** The experimental group receives 4 stereotactic fractions. The historic control group has received 10 fractions (standard of care) with approximately a biological equivalent dose.

**Main study endpoint:** The primary endpoint is overall survival after re-irradiation. The key secondary endpoint is progression free survival. Other secondary endpoints are recurrence patterns, toxicity, HRQoL and anti-edema treatment.

**Nature and extent of the burden and risks associated with participation, benefit and group relatedness:** For the patients included in the study, no individual benefits and no known risks are associated with the tests performed. To reduce patients' burden, hospital visits are mainly limited to standard follow-up. Most additional follow-up assessments will be performed by telephone or by self-administered forms. We use the EQ-5D-5L at baseline and 2, 4 and 6 weeks after start of radiotherapy and thereafter the QLQ-C15-PAL to assess HRQoL. The questionnaires could be conducted in less than 10 minutes at home. Additionally, at the same time points patients will be asked about adverse events, anti-edema treatment and reminded to complete their HRQoL assessments during a phone call of a few minutes. Furthermore, technical data, including MRI, CT and radiation treatment plans, acquired in standard care will be utilized.

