### **8.1.3 HRQoL in arm 1**

HRQoL will only be assessed in the experimental group. Reasons for missing baseline and follow-up questionnaires will be assessed. Linear Mixed Effects models will be used for regression analyses of HRQoL. In addition, the repeated measures of the EQ-5D-5L, QLQ-C15-PAL and BN20+2 functional and symptom scales will be assessed by time to deterioration (TTD) analyses. The time until definitive HRQoL score deterioration (TUDD) is defined as time from inclusion to a first deterioration of the score with a minimal clinically important difference (MCID) of at least 10 points as compared to the baseline score. With no further improvement of more than the MCID as compared to the baseline score or if the patient dropped out after deterioration, resulting in missing data. According to the construction of the HRQoL scores, deterioration corresponds to an increase (e.g., for symptomatic scales of the EORTC questionnaires and EQ-5D-5L) or a decrease (e.g., for functional scales) of the score.

Patients with no score available are excluded from the time-to-deterioration analyses.

Patients with no baseline score are usually censored at baseline and those with no follow up scores but with a baseline score are censored one day after baseline. Patients with no deterioration before drop-out from the study, including death, are censored at the time of last HRQoL questionnaire completion or last follow-up.

The TUDD estimation will be calculated using the Kaplan-Meier method and described using median and 95% CI.

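### The EORTC questionnaires start at week 13, so time to deterioration from baseline cannot be estimated on the current schedule; the EQ-5D-5L rule also does not fit its scores

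*Protocol*

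**What the plan says.** **Schedule.** The protocol Summary states: "We use the EQ-5D-5L at baseline and 2, 4 and 6 weeks after start of radiotherapy and thereafter the QLQ-C15-PAL to assess HRQoL". Section 6.2 sets the contacts "at baseline and at 2, 4, 6, 13, 26, 39, and 52 weeks from the start of ReRT or until disease progression" and assigns the instruments: "During the first 6 weeks HRQoL will be assessed using the EQ-5D-5L", and after that "At subsequent time points QLQ-C15-PAL and BN20+2 will be completed digitally or on paper". Section 6.3.1 places the EORTC forms after the EQ-5D-5L period, at three-monthly intervals once radiotherapy has ended. Section 9.3 also puts the QLQ-C15-PAL after week 6. Table 3 ticks HRQoL at baseline but names no instrument. Nothing in the protocol places an EORTC form at baseline.

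**Analysis.** Section 8.1.3 plans linear mixed models and, in addition, a time-to-deterioration analysis of EQ-5D-5L, QLQ-C15-PAL and BN20+2. Time runs from inclusion, and the event is a worsening by a "minimal clinically important difference (MCID) of at least 10 points as compared to the baseline score". On missing data it says: "Patients with no baseline score are usually censored at baseline". Patients with no score at all are excluded. The result is to be a Kaplan-Meier median with a 95% CI. Deterioration means an increase for some scales ("e.g., for symptomatic scales of the EORTC questionnaires and EQ-5D-5L") and a decrease for functional scales.

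**EQ-5D-5L content.** Section 6.3.1 describes five dimensions with five levels each, plus a visual analogue scale (VAS). No index or sum score is named.

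**The concern.** The analysis needs a pre-treatment EORTC score that the schedule does not collect. A later statistical analysis plan could choose another analysis, but it could not recover a baseline form that was never completed, and each patient enrolled under the present schedule loses that reference for good. At stake are the change-from-baseline results for all cancer-specific and brain-specific scales, within the secondary objective of describing HRQoL in the experimental arm.

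The second, smaller problem is that one threshold and one direction are carried over to the EQ-5D-5L without saying which of its scores is analysed.

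**Working it through.** The protocol gives no sample size, event count or power for HRQoL, so there is no planned figure to reproduce. The check applies the section 8.1.3 rules to the section 6.2 schedule.

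**1. Instruments by visit (sections 6.2 and Summary)**

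| Week | 0 | 2 | 4 | 6 | 13 | 26 | 39 | 52 |
|---|---|---|---|---|---|---|---|---|
| EQ-5D-5L | yes | yes | yes | yes | – | – | – | – |
| QLQ-C15-PAL, BN20+2 | – | – | – | – | yes | yes | yes | yes |

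**2. EORTC time to deterioration**

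- The event needs a score at a later visit and a score at baseline. The second does not exist on this schedule, so no event can be recorded.
- A patient with at least one EORTC score but no baseline score is censored at time 0.
- A patient with no EORTC score is excluded.
- For patients on the schedule: events = 0 and person-time = 0. The Kaplan-Meier curve has no follow-up, so neither the median nor its CI exists.

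**3. How many patients**

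- Arm 1 is to reach 66, of whom 13 come from trial A (section 3): 66 − 13 = 53 to be recruited under the current schedule, or 53/66 = 80%.
- The earlier protocol of trial A is not shown, so the baseline forms of the other 13 are unknown.

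**4. EQ-5D-5L against the rule of an increase of at least 10 points**

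- *Single dimension, levels 1 to 5:* largest change 5 − 1 = 4. Ten points cannot be reached.
- *VAS:* ten points can be reached if the scale runs from 0 to 100. If higher means better health, the rule counts improvement as deterioration. The protocol states neither the range nor the direction, so both are assumptions.
- *Unweighted sum of the five levels, 5 to 25 (not named in the protocol):* largest change 20. An increase of 10 is possible when the baseline sum is 15 or less, which holds for 1753 of the 5^5 = 3125 profiles (56%), and the direction is right.

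**5. What the EORTC analysis would have if a baseline were collected**

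Section 4.4 expects a 12-month event rate of 0.7. With exponential survival (assumption), S(w) = 0.3^(w/52):

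| Week | S | Alive of 66 |
|---|---|---|
| 13 | 0.74 | 49 |
| 26 | 0.55 | 36 |
| 39 | 0.41 | 27 |
| 52 | 0.30 | 20 |

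Fewer would be assessed, because questionnaires stop at progression. This shows what the repair could deliver. It does not measure the defect, since the first EORTC follow-up stays at week 13 either way.

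**The case against.** **Only one supplementary analysis is affected.** The objective is to describe HRQoL in one arm, with no comparator, test or sample size. Section 8.1.3 names mixed models first, and these can still describe EORTC scores from week 13 to week 52. This stands, and it limits the weight of the point. A reader might infer that the whole HRQoL objective is lost; the protocol does not support that. The mixed models still cannot show EORTC change from before treatment.

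**Not all of arm 1 is shown to lack a baseline.** A reader might infer that every arm 1 patient does. The protocol is silent on the 13 trial A patients, so the statement holds only for those on the current schedule. The Summary is also the only place that names the baseline instrument explicitly, and the censoring rule is qualified as the usual one. Neither repairs the analysis: no EORTC form is placed at baseline anywhere, and no other reference visit is offered.

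**The EQ-5D-5L score may be left to the analysis plan.** The choice of score may be. A reader might infer that the EQ-5D-5L analysis is invalid under any reading. That goes too far: a level sum would fit both the threshold and the direction, and the VAS criticism depends on an assumed direction. What stands is that the rule does not fit the dimensions as described, and that the score it would fit is not mentioned.

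**Two further inferences are not supported.** Stopping the EQ-5D-5L at week 6 is explained by its short completion time and fits the protocol's stated aim of limiting burden, so it is not an error. Censoring deaths here, while section 8.1.4 treats death as a competing risk for late toxicity, is a choice open to debate for a descriptive endpoint, not a contradiction.

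**Conclusion.** The point holds for the EORTC scales. Schedule and analysis are incompatible: patients on the current schedule yield 0 events and 0 follow-up, so the planned median time to deterioration and its CI cannot be produced for QLQ-C15-PAL or BN20+2. This follows from the protocol's own text without any assumption, and it concerns 53 of the 66 planned arm 1 patients; the status of the other 13 is unknown.

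For the EQ-5D-5L the supportable conclusion is narrower. The 10-point increase cannot occur on a single dimension, is reversed on the VAS if higher means better health (assumption), and works only for a sum score that the protocol does not name. Score, direction and threshold need to be stated.

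The consequence is limited to a single-arm descriptive secondary endpoint. OS, PFS and the non-inferiority decision do not depend on it. It is nevertheless worth correcting promptly, because a missed baseline form cannot be recovered afterwards.

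**What to change.** - **Sections 6.2, 6.3.1, Summary and Table 3:** add QLQ-C15-PAL and BN20+2 at baseline, alongside the EQ-5D-5L, for all further patients, and name the instrument at each visit in Table 3.
- **Section 8.1.3, EORTC:** run time to deterioration only in patients with an EORTC baseline score and report how many that is. For the others, describe EORTC scores from week 13. Check whether the 13 trial A patients completed an EORTC form at baseline and state the answer.
- **Section 8.1.3, EQ-5D-5L:** name the score or scores analysed and give each its own direction and threshold.

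If the sponsor does not want the extra baseline form, dropping the EORTC time-to-deterioration analysis or naming another reference visit would also remove the contradiction, but would give up change from before treatment.

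**Cost:** amended wording and one extra questionnaire pack of 37 items at an existing contact. The protocol puts questionnaire completion at under 10 minutes. Patients already treated without an EORTC baseline cannot be recovered for this analysis.

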**Table 3. Treatment and follow-up procedures per patient in experimental arm 1**

|                                     | Baseline | Treatment and follow-up period (weeks after first fraction) |   |   |    |    |    |    |
|-------------------------------------|----------|-------------------------------------------------------------|---|---|----|----|----|----|
|                                     |          | 2                                                           | 4 | 6 | 13 | 26 | 39 | 52 |
| Baseline characteristics and intake | X        |                                                             |   |   |    |    |    |    |
| Hypofractionated RT                 |          | X                                                           |   |   |    |    |    |    |
| HRQoL                               | X        | X                                                           | X | X | X  | X  | X  | X  |
| Molecular analysis                  | X        |                                                             |   |   |    |    |    |    |
| Upload information/imaging          | X        |                                                             |   |   |    | X  |    | X  |

### 6.3 Study procedures retrospective Arm 2

The available data for the retrospective control group (arm 2) will be selected from the retro-RISinG trial.

#### 6.3.1 Health Related Quality of Life (arm 1)

Health Related Quality of Life (HRQoL) will be assessed via 3 questionnaires: EQ-5D-5L, EORTC QLQ-C15 PAL and EORTC-QLQ-BN20+2.

EQ-5D-5L is a validated measure of health status developed by the EuroQol Group in order to provide a simple, generic measure of health for clinical and economic appraisal [36, 37]. It consists of a descriptive system comprising 5 dimensions (mobility, self-care, usual activities, pain/discomfort, anxiety/depression) at 5 levels and the EQ Visual Analogue scale. This tool is used for the HRQoL measurement during the first 6 weeks after therapy start, since it takes only a few minutes to complete.

Subsequently, HRQoL will be determined using the EORTC QLQ-C15 PAL questionnaire [38] and QLQ-BN20+2 questionnaire [39] every 3 months after finishing radiotherapy treatment. The QLQ-C15 PAL is a validated general core QoL assessment tool which is developed for (near) palliative cancer care patients. The tool consists of 15 questions: 2 multi-item functional scales (physical and emotional functioning), 2 multi-item symptom scales (fatigue and pain) along with 5 single-item symptom scales (nausea/vomiting, dyspnea, insomnia, appetite loss, and constipation), and 1 final question referring to overall QoL. Patients rate each question/item on a numeric scale from 1 (not at all) to 4 (very much), with the exception of overall QoL, which was rated from 1 (very poor) to 7 (excellent).

The QLQ-BN20+2 includes the QLQ-BN20 questionnaire that has been validated for use in patients with primary brain malignancies. In addition, two scales for concentration and memory were added which were omitted in the abbreviated QLQ-C15-PAL. The QLQ-BN20 consists of 20 questions: 7 single-item symptom scales (headaches, seizures, drowsiness,

hair loss, itchy skin, leg weakness, and bladder control), along with 4 multi-item scales (future uncertainty, visual disorder, motor dysfunction, and communication deficit). The QLQ-BN20+2 was first described by Caissie et al. and validated by Nguyen et al. in patients with brain metastases [39, 40].

These questionnaires consist in total of 37 assessments instead of 50 assessments when using the QLQ-C30. This aims to minimize patients' burden and increase the chance of maintaining follow-up as patients progress through their disease course [39].

### **6.3.2 Procedures for Assessing Adverse Events (arm 1 and 2)**

Early and late AEs associated with radiotherapy will be recorded or retrieved. Data includes (but is not limited to) central nervous system necrosis, edema, seizure, headache, fatigue, nausea and radiation dermatitis. Toxicity will be assessed according to CTCAE version 5.0. See Appendix 2 for toxicity grade per term.

## **6.4 Withdrawal of individual subjects**

Subjects can leave the study arm 1 at any time for any reason if they wish to do so without any consequences. The investigator can decide to withdraw a subject from the study for urgent medical reasons. If a patient is going off protocol treatment, the reason should be documented. Patients are not obligated to specify the reason of withdrawal.

## **6.5 Replacement of individual subjects after withdrawal**

In section 4.4 the sample size calculation for this study is given. Therefore, an inclusion of 65 subjects per study group is aimed to generate a total of 130 patients. If a subject in arm 1 discontinues from the study prematurely the reason, if given, must be fully evaluated and recorded appropriately.

If a patient who has signed informed consent withdraws for any reason before randomization, the patient will be replaced. These patients are not included in the statistical analysis. After randomization, patients withdrawing because of any reason will not be substituted by additional patients. Patients withdrawn from the trial retain their identification codes (e.g. randomization number), if already given. New patients must always be allotted a new identification code.

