### 3. STUDY DESIGN

The original 2019 RISING-trial (RISING trial A) was designed as an open label, randomized, non-inferiority, phase III trial with 1:1 allocation for 130 patients. In this trial 13 patients were included in the experimental arm and 16 patients were included in the control arm. The updated 2023 RISinG trial (RISING trial B) is designed as a phase II, multi-center, clinical trial with a historic control group. The additional recruitment period of this phase will be approximately 30 months with an active follow-up time of 12 months.

The 13 patients of the RISING trial A will be supplemented until a total of 66 patients is reached. These patients fulfilling the inclusion criteria will get the following treatment:

- Hypofractionated radiotherapy with SIB in 2 weeks  
4 fractions of 7.5 Gy SIB to the GTV  
And 4 fractions of 5.5 Gy to the CTV (GTV + 5mm margin).

We will compare the survival of this group with a retrospective control group of patients, subtracted from the retro-RISinG registry study, a multi-center retrospective nation-wide population based cohort study, in which details of patient-, tumor- and treatment-related data of all patients with a recurrence of a primary brain tumor since January 2002 up to December 2022 in the Netherlands will be collected. We will select 99 matched patients in total with the following treatment:

- Moderately hypofractionated radiotherapy in 2-3 weeks  
10 fractions of 3.5 Gy to the CTV (GTV + 5 mm margin)

An overview of the target volume definitions and dose prescriptions is presented in table A3 in section 1.8 of the Appendix.

This control group will be matched to the patients in the experimental arm on an individual level for:

1. Age;
2. Gender;
3. WHO-grade primary tumor;
4. Time interval in between first radiation and re-irradiation;
5. MGMT-status.

[figure not shown]

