#### 8.1.1 OS and PFS

All statistical tests for the efficacy endpoint OS and PFS will be performed according to intention-to-treat (ITT) principle, which is the most unbiased method. Considering the trial being a non-inferiority trial, which is more sensitive to bias, a secondary per-protocol (PP) analysis will be done for OS [43]. The PP analyses will be performed on a “subset of patients who complied sufficiently with the protocol, such as exposure to treatment, availability of measures and absence of major protocol violations” according to the ICH E9 guidelines. The ITT analysis includes all participants. Start date of ReRT will be used as time is 0. Patients not known to have died during the study will be censored for OS at the day they were last known to be alive. Patients free from progression and alive at the last visit will be censored for PFS at the day of last assessment. Endpoints are measured from the first date of re-irradiation.

Distributions of OS and PFS will be estimated by the Kaplan-Meier method. The OS rates at one year, PFS rates at six months and medians of OS and PFS will be presented with two-sided 95% confidence interval(CI) computed using the log-log transformation.

To minimize the effect of confounding when estimating the difference between the treatment and retrospective control group, stabilized inverse probability of treatment weighting (SIPTW) using propensity scores will be applied when comparing the groups on OS and PFS.

Propensity scores will be estimated using logistic regression including important covariates for OS and PFS: primary histology, GTV, KPS and age.

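### Section 6.5 ends replacement and exclusion only at randomization, so the 53 arm 1 patients enrolled in trial B have no cut-off, and the rule conflicts with the ITT statement in 8.1.1

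*Protocol*

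**What the plan says.** Section 6.5 has two limbs. The first: "If a patient who has signed informed consent withdraws for any reason before randomization, the patient will be replaced", followed by "These patients are not included in the statistical analysis". The second: "After randomization, patients withdrawing because of any reason will not be substituted by additional patients". Randomization is the only event that separates them.

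Section 3 describes the current study (trial B) as one that "is designed as a phase II, multi-center, clinical trial with a historic control group". On arm 1 it says: "The 13 patients of the RISING trial A will be supplemented until a total of 66 patients is reached". Section 9.2 goes from consent to collection of baseline characteristics with no randomization step.

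Section 6.4 governs who may leave: "Subjects can leave the study arm 1 at any time for any reason if they wish to do so without any consequences", and "The investigator can decide to withdraw a subject from the study for urgent medical reasons".

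Section 8.1.1 sets the efficacy population and the time origin: "The ITT analysis includes all participants. Start date of ReRT will be used as time is 0". It does not define a participant and does not refer to 6.5.

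**The concern.** Section 6.5 is carried over from the randomized trial A. For a patient enrolled in trial B the replace-and-exclude limb never ends and the no-substitution limb never begins. A rule on who belongs to the primary analysis is therefore stated without a working cut-off, and it disagrees with 8.1.1.

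The direction of any error matters because this is a non-inferiority comparison. If someone who has begun re-irradiation withdraws and is replaced by someone who completes it, arm 1 is selected on something that happened after time zero. Of the 99 controls, 83 are historic patients chosen because they had the 10 x 3.5 Gy schedule, and the other 16 were randomized in trial A, so none is subject to an open-ended rule. If withdrawal goes with poor prognosis, the arm 1 hazard is lowered and a false declaration of non-inferiority becomes more likely.

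**Working it through.** **Step 1. Who is affected.** Arm 1 totals 66, of whom 13 come from trial A (sections 3 and 4.1). 66 - 13 = 53 patients have no randomization date. The 13 do, so the rule works for them. Arm 1 thus pools patients under two different rules.

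**Step 2. The two sections side by side, for a trial B patient.**

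| Patient withdraws | Section 6.5, literal | Section 8.1.1 |
|---|---|---|
| After consent, before the first fraction | Replaced, not analysed | A participant, perhaps, but with no time zero |
| After the first fraction | Still not randomized: replaced, not analysed | In the ITT set, with a valid time zero |

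The second row is a direct contradiction. The first row shows that counting every consented patient does not work either, because OS and PFS run from the first date of re-irradiation. That interval exists: consent precedes radiotherapy preparation (9.2), and up to 3 weeks may pass between planning MRI and first fraction (Appendix 1.7).

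**Step 3. The plan's own sample size.** Inputs from section 4.4: assumed HR 0.90, margin 1.4, one-sided alpha 0.05, power 0.80, allocation 40%/60%, event proportion 0.8.

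Events = (1.645 + 0.842)² / [0.4 x 0.6 x (ln(0.90/1.4))²] = 131.96, rounded up to 132. N = 131.96 / 0.8 = 164.95, rounded up to 165. This reproduces the stated 165 (99 + 66). Correcting 6.5 does not change it.

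**Step 4. Conditional size of the effect.** The protocol gives neither a withdrawal rate nor the prognosis of those who withdraw, so both are assumed and varied. Set-up: 66 versus 99 patients; exponential survival; control median OS 9 months (section 1.1 cites 7.7 to 11.5); follow-up 12 to 42 months; the same share of frailer patients in the source population of both arms, all replaced by ordinary patients in arm 1 and none in the control arm; unweighted Cox model; non-inferiority if the upper two-sided 90% limit is below 1.4. Type I error is taken at a true HR of 1.4.

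| Withdrawers | Hazard relative to others | One-sided type I error | Estimated HR when truth is 0.90 |
|---|---|---|---|
| Any share | 1 | about 5% | 0.90 |
| 5% | 1.5 | about 6% | about 0.89 |
| 3% | 3 | about 6% | not tabulated |
| 5% | 3 | 8% to 9% | about 0.87 |
| 10% | 3 | about 12% | 0.83 to 0.84 |

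Without replacement, type I error is 5% to 6% in this set-up. In patient numbers, 3%, 5% and 10% of 66 are 2.0, 3.3 and 6.6. The simulation applies replacement to all 66; only 53 lack a cut-off (53/66 = 80%), so at a given rate the figures lean high.

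**The case against.** The strongest reply is that nobody intends the harmful reading. It would make the second limb of 6.5 void for trial B. Section 8.1.1 contrasts ITT with a secondary per-protocol analysis, which presupposes that non-compliers stay in ITT. Section 6.6 provides, with consent, for questionnaires and record checks after withdrawal from treatment. Section 8.1.4 analyses toxicity in everyone with at least one fraction. Together these point to a pre-treatment cut-off. This stands: removal of treated patients is something the literal text permits, not a declared plan. It does not rescue 6.5, because none of these sections overrides it or supplies the missing event.

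A reader might infer that treated patients who do badly can simply be removed from the primary analysis. The documents do not support that. The rule acts only on withdrawal, so a patient who deteriorates or dies without withdrawing stays in. Coming off treatment (6.6) is also not the same as leaving the study. All fractions fall within 2 weeks (Appendix 1.5), so the window for withdrawal between fractions is short.

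A reader might also assume that withdrawals are mostly due to deterioration or toxicity. Section 6.4 allows investigator withdrawal for urgent medical reasons but gives no frequency, and patients need not state a reason. The propensity weighting in 8.1.1, which includes KPS, GTV and age, might absorb part of a frailty imbalance and is not modelled above.

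Finally, exact analysis sets are often left to the SAP. That would answer a silence. Here the protocol states a rule, and the rule refers to an event that does not occur.

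**Conclusion.** The wording defect is certain: for 53 of 66 arm 1 patients, section 6.5 has no cut-off and conflicts with 8.1.1. Its consequence is conditional. If treated withdrawers were in fact replaced and excluded, type I error at the 1.4 margin would run from about 5% (ordinary prognosis) through about 6% to about 12% (10% withdrawers at 3 times the hazard), always in the direction of non-inferiority when withdrawers fare worse. These figures rest on assumed withdrawal rates and hazards, exclusion of every withdrawer, and no weighting. They show what the loose wording could cost and do not predict a bias. This is a should-fix consistency error. A claim that the plan sets out to remove treated patients with poor outcomes would go beyond the text.

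**What to change.** In 6.5, for patients enrolled in trial B, replace randomization with the first fraction of re-irradiation, which is already time zero in 8.1.1. Consented patients who withdraw before it may be replaced; they are listed but not analysed. From the first fraction on, every patient stays in the primary OS and PFS set and is not replaced. State the same set in 8.1.1. Registration would also give a cut-off, but it would keep patients with no time zero in the set.

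Leave the 13 trial A patients under their randomization rule, which works, and report any who were randomized but did not start re-irradiation. Imposing an at-least-one-fraction set on them now could drop such patients after the fact.

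The cost is a wording amendment to two sections. The sample size stays at 165 and no procedure changes. It should be made before further withdrawals have to be classified and before outcomes are analysed, so that the choice cannot be called data-driven.
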